#### Secondary outcomes

The secondary outcomes of this study are described in Table 2. Self-reported data on all secondary outcomes will be collected at baseline, and at 6- and 12-months from baseline assessment, via online (electronic) questionnaires (see Additional file 3, Additional file 4). In addition, self-reported data on pain intensity, self-management behaviours, and medication use will be assessed on a fortnightly basis during the 12-month follow-up period, collected via a repeating online (electronic) questionnaire specifically designed for this study (see Additional file 5).

**Table 2 Tab2:** Secondary outcomes

Secondary outcome	Measurement tool	Description
Self-reported physical activity levels	Global Physical Activity Questionnaire (GPAQ) [31]	The GPAQ assesses intensity-specific physical activity participation in 3 domains (activity at work, travel to and from places, recreational activities), and sedentary behaviour [31].
Objective physical activity levels	Axivity tri-axial accelerometer [32], assessed over a 7-day period	The device accurately estimates how physically active a person has been throughout the day using an accelerometer. The outcomes are overall physical activity, categorised according to intensity (sedentary, light, moderate, vigorous) and quantified as the average counts per minute of acceleration during the time the accelerometer is worn.
Function	Patient Specific Functional Scale (PSFS) [33]	At baseline, participants will be asked to self-select three activities they have difficulty performing due to their LBP. Each activity will be scored on an 11-point scale at each timepoint, with 0 representing ‘unable to perform activity’ and 10 representing ‘able to perform activity at the same level as before injury or problem.’ The scores for the three activities will be summed, giving a total score ranging from 3 to 30.
Pain intensity (i.e., mean intensity of LBP over the past fortnight)	Numerical Rating Scale (NRS) [34]	The NRS is an 11-point scale, scored on a scale of 0 to 10, with 0 representing ‘no pain’ and 10 representing ‘worst possible pain.’
Disability	Roland–Morris Disability Questionnaire (RMDQ) [35]	The RMDQ consists of 24 items and total scores range from 0 to 24, with higher scores indicating higher disability levels.
Quality of life	Assessment of Quality of Life questionnaire (AQoL-8D) [36, 37]	The AQoL-8D consists of 35 items across 8 dimensions, with higher scores within each dimension corresponding to poorer quality of life. Utility weighted AQoL-8D scores will be used to estimate quality-adjusted life years (QALYs) for the cost-effectiveness analysis [38].
Self-management behaviours	Questionnaire specifically designed for this study	Examples of self-management behaviours will include, but are not limited to, the use of heat packs or hot showers for LBP, massage (not delivered by a professional), brace or support strapping/tape, topical creams/gels, physical activity and exercise, relaxation, meditation, mindfulness techniques, and walking aids specifically used to manage LBP.
Medication use	Questionnaire specifically designed for this study	Data on the use of medications for managing LBP, including type (i.e., paracetamol, non-steroidal anti-inflammatory drugs, opioids), dosage, and whether the medication was prescribed by a medical or health professional, will be collected on a fortnightly basis.
Sleep quality	Pittsburgh Sleep Quality Index (PSQI) [39]	The PSQI is an 18-item self-reported questionnaire assessing sleep disturbances in the last month. The total score is composed of a sum of scores in 7 different domains and ranges from 0 to 21, with higher scores indicating poorer sleep quality.
Attitudes regarding use of pain medications	Short-form Pain Medication Attitudes Questionnaire (PMAQ-14) [40]	The PMAQ-14 consists of 14 items across 7 areas of concern for users of pain medications (addiction, need, scrutiny, side effect, tolerance, mistrust of doctors, withdrawal). Each item is scored on a 6-point scale with 0 representing never true and 5 representing always true.
Beliefs about back pain	Back Beliefs Questionnaire (BBQ) [41]	The BBQ consists of 14 items and total scores range from 9 to 45, with lower scores indicating more negative beliefs about back pain.

### Recruitment

#### Participant identification

Physiotherapists from the outpatient musculoskeletal physiotherapy departments of participating hospital sites will identify (all) patients who are within 1–2 weeks of their anticipated discharge from physiotherapy treatment for chronic LBP. The physiotherapist will introduce the study to all candidate patients. For patients indicating interest in participation, their contact details will be provided to the research team. The research team will phone the potential participant to provide them with further information about the study, including the study documents. Those who confirm their interest in the trial will be invited to take part in the consent procedures with a research team member, which will ideally occur within 1–2 weeks prior to discharge from treatment. De-identified demographic data (age, sex) and LBP pain scores at discharge from treatment (assessed with the NRS) will be collected from all candidate patients, irrespective of their interest or provision of consent. Data will be used to assess selection bias and target population reach.

#### Consent and screening

Depending on participant preference, consent procedures will occur face-to-face at the hospital site or remotely via an online consent form. For participants choosing to consent remotely, a research team member will provide support via phone call or video-conferencing software. During consent procedures, a research team member will discuss the study Participant Information Sheet and Consent Form with the participant (see Additional file 6). Potential participants who agree to take part in the study will be asked to sign a paper or online version of the study consent form. After signing the study consent form, the participant will be enrolled into the study and immediately assigned a unique participant code, which will be used on all study documents to protect their privacy. In addition, the research team will request written consent from participants to access their Medicare Benefits Schedule and Pharmaceutical Benefits Scheme claims data.

After consent procedures are completed, participants will be formally screened for eligibility and medical safety. For participants who meet the study eligibility criteria and are considered medically safe to participate in the trial, a research team member will phone the participant to invite them to take part in the baseline assessment. In accordance with standard Get Healthy Service® registration requirements [22], participants who are identified as requiring additional medical clearance will be referred to seek written recommendations from their medical doctor prior to randomisation.

### Baseline assessment

Depending on participant preference, baseline assessment will occur face-to-face at the hospital site with a research assistant, or remotely. For participants completing baseline assessment remotely, a research team member will be available to provide support via phone call or video-conferencing software. Participants will be required to complete an online (electronic) baseline questionnaire to record demographic and anthropometric data (age, height, weight), and the study outcomes (see Additional file 3). In addition, participants will be given a tri-axial accelerometer (Axivity) to wear for 7 consecutive days on their right thigh. During the 7-day period, participants will be asked to document any physical activities or exercises completed in a paper-based logbook (see Additional file 7). After 7 days, participants will return the accelerometer and logbook to the research team via a pre-paid reply envelope. At baseline assessment, all participants will also receive a paper-based weekly diary (see Additional file 8) to document any adverse events which may occur during the intervention period (6 months) - see below. For participants who complete the baseline assessment at the hospitals, the online baseline questionnaire will be completed on-site and the research team member will directly attach the accelerometer onto the participant’s thigh. For participants who complete the baseline assessment remotely, they will receive a link to the online baseline questionnaire via SMS or email, and any relevant study documents and equipment will be posted to them. The participant will receive a detailed sheet with labelled images and instructions on how to self-attach the accelerometer device (see Additional file 7). As required, a research team member will be available to provide support for any baseline assessment procedures, via phone call or video-conferencing software.

### Randomisation

After baseline assessment has been completed and the participant has been discharged from treatment, participants will be randomised with 1:1 allocation ratio to either the support system or usual care group. Treatment allocation will be performed using a computer-generated random allocation schedule operated by a remote unblinded researcher to ensure concealment. As participants will be randomised after discharge from treatment, with minimal potential for treatment contamination, randomisation will be at participant level. Randomisation will be by random permuted blocks of 4 and 6. Participants will be notified of their allocation via phone call from an unblinded research assistant. Select members of the research team will be unblinded to treatment allocation (i.e., main trial co-ordinator, the designated investigator managing referrals to the Get Healthy Service®, unblinded statistician monitoring trial safety, health coaches and agents from the Get Healthy Service®). Otherwise, all other research team members will remain blinded to treatment allocation. Participants will not be blinded to group allocation.

### Usual care group

Participants in the usual care group will only receive the standard care delivered by their physiotherapist at discharge from outpatient treatment from participating hospitals. Usual care commonly involves the provision of advice, education, and a home-based exercise program, with no further intentional follow-up appointments arranged. Standard usual care at discharge may also involve referral to local community exercise providers, although the availability of these programs is highly variable across hospital sites and community regions. Participants in the usual care group will be able to continue seeking other forms of health care and treatments as desired.

### Intervention group (support system involving referral to the Get Healthy Service®)

Similar to the usual care group, participants in the intervention group will receive the standard care delivered by their physiotherapist at discharge from outpatient treatment and will be able to seek other forms of health care and treatments as desired. In addition, participants in the intervention group will be referred for enrolment into the Get Healthy Service® *Standard Coaching* module (health coaching program) with a physical activity goal.

#### Referral to the Get Healthy Service®

All participants who are randomised to the support system will be referred to the Get Healthy Service® via the same structured referral pathway. A designated investigator (clinician) at each hospital will manage the referral process for the site. The designated investigator will enter the contact information of participants randomised to the support system group into a digital referral channel on the Get Healthy Service® website, via an online form specifically designed for the study. Evidence of medical clearance will be provided to the Get Healthy Service® via a secure file transfer program, when required. Upon receipt of the referral, a staff member (intake specialist) from the Get Healthy Service® will phone trial participants to complete the registration call. During the registration phone call, the intake specialist will enrol the participant into the *Standard Coaching* module. After successful enrolment, an assigned health coach will phone the participant to commence the health coaching program.

#### Structure of the Get Healthy Service®

The Standard Coaching module will be delivered in accordance with its current features and specifications, but with some adaptation to align the content of the module with best practice for management of LBP. Participants will be offered up to 10 individually tailored phone-based health coaching sessions over a 6-month period. Sessions will be approximately 17 minutes in duration and will be led by health coaches with university-qualifications in allied health (i.e., dietetics and/or exercise physiology). All health coaches are required to complete training in health coaching, predominately acquired through HealthChange® Australia (2-day Core Training program) [42], as well as internal training by clinical specialists as required. The sessions will be delivered to participants by their personal health coach, selected to match their goals and personal preference (i.e., male or female coach). The frequency of sessions will be tapered over the 6-month period according to each participant’s preference and progress through the program. The initial health coaching session will focus on mutually establishing the participant’s physical activity goals, as well as other health-related goals (i.e., reducing weight, achieving a healthy diet, reducing alcohol consumption) that are meaningful to the participant.

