#### Fidelity of the health coaching program

The Get Healthy Service® conducts internal health coaching call audits for 1% of all calls per month carried out by the service. The audits are based on the following key criteria: security and privacy, clinical best practice, health coaching (i.e., effective utilisation of health coaching skills and techniques), call etiquette, documentation. Further, in the initial period of study implementation, the Get Healthy Service® will perform targeted auditing of health coaching calls delivered for participants specifically referred from the trial. The purpose will be to ensure that appropriate clinical best practice and high quality referral processing are achieved.

The research team will assess fidelity of the health coaching program by evaluating the following: (i) number of participants randomised to the support system who successfully establish a physical activity goal at commencement of the health coaching program; (ii) total number of health coaching sessions received per participant; (iii) number of participants who complete the Get Healthy Service® *Standard Coaching* module, where completion will be defined as receiving the 10 allocated health coaching sessions or achievement of participant goals. Data will be collected by the Get Healthy Service® and provided to the research team.

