### Sample size calculation

The sample size is that required to detect a clinically meaningful between-group difference in the primary outcome, i.e., the total number of encounters with hospital, medical, and health services for LBP [44]. A total of 374 participants (*n* = 187 per group) will be recruited. The study will have 90% power to detect as significant, at the 5% level, a 30% difference in the rate of using hospital, medical, and health services for LBP between groups (i.e., an Incidence Rate Ratio of 0.70 using negative binomial regression analysis) over the 12-month study period. The 30% difference in the rate of using hospital, medical, and health services for LBP is based on our research of patients’ perceptions of a clinical worthwhile effect of interventions for LBP [45]. Estimates were based on a base rate exposure (β0) of 0.2 [total of 2 care-seeking events in the usual care group per fortnight (data from pilot)], assuming a correlation of 0.3 (R^2^ = 0.09) between covariates and predictor (treatment), using negative binomial regression model (G*Power® software) [46]. Estimates allow for a loss to follow-up of 10%.

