### Statistical analysis

The total number of encounters with hospital, medical, and health services for LBP per person, over 12 months from baseline assessment, will be analysed using negative binomial regression to estimate the between-group difference in the rate of using hospital, medical, and health services for LBP at 12-month follow-up. Negative binomial regression takes into account individual follow-up time, frequency of using hospital, medical, and health services for LBP, non-normal distribution over time, and non-independence of repeated measures [44]. The effect of baseline pain and disability levels, number of previous treatments, symptom length, co-morbidities, and age will be accounted for in the model. The effect of group allocation on continuous outcomes (e.g., physical function, physical activity) will be assessed using linear regression models. All analyses will be performed by intention to treat.

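### The stated primary model and sample size make no allowance for clustering by health coach in the support arm, and coach identity is not among the listed service data

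*Protocol article*

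**What the plan says.** All references are to the protocol article.

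- **Delivery.** Under *Referral to the Get Healthy Service*, an assigned coach starts the programme with each enrolled participant. Under *Structure of the Get Healthy Service*: "The sessions will be delivered to participants by their personal health coach, selected to match their goals and personal preference". Coaches come from dietetics and/or exercise physiology. The *Usual care group* section describes no coach.
- **Content.** Table 3 has coaches help participants decide whether further care for back pain is needed, and advise on when imaging is warranted. Care visits and imaging both count towards the primary outcome.
- **Data from the service.** *Fidelity of the health coaching program* lists three items: whether a physical activity goal was set, the "total number of health coaching sessions received per participant", and module completion. Coach identity is not listed.
- **Analysis.** *Statistical analysis* specifies a negative binomial regression of each person's 12-month total with named baseline covariates. The only dependence it mentions is in the phrase "and non-independence of repeated measures". There is no coach term.
- **Sample size.** The target is 374 in all, 187 in each arm. On power, the section states: "The study will have 90% power to detect as significant, at the 5% level, a 30% difference in the rate". The calculation allows for covariates and 10% loss, but not for clustering.
- **Randomisation** is individual. The reason given is low contamination risk; clustering by provider is not discussed.

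**The concern.** Participants who share a coach share that coach's style and advice, and part of that advice concerns the behaviour counted in the primary outcome. If coaches differ in their effect, outcomes within a coach's caseload are positively correlated, in one arm only. The negative binomial dispersion parameter absorbs variation between persons. It does not absorb covariance between different persons with the same coach. The reported standard error of the rate ratio would then be too small.

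The interval for the primary result is at stake, as is the power of any analysis that uses the correct standard error. The trial also aims to inform scale-up, and whether an effect rests on a few coaches bears on that. A model can be added later, but it needs the identifier, which is best requested when the data transfer is set up.

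**Working it through.** **The plan's own figure.** The inputs are "an Incidence Rate Ratio of 0.70 using negative binomial regression analysis", 90% power, 5% level (two-sided assumed), a base rate of 0.2, R² = 0.09 and 10% loss. For a Poisson-type Wald calculation with 1:1 allocation:

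N = (1.960·√V0 + 1.282·√V1)² / [T × 0.2 × (ln 0.70)² × 0.91], with V0 = 4 and V1 = 2 + 2/0.70 = 4.857, then divided by 0.9 for loss.

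Mean exposure T and the dispersion are not stated, so 374 cannot be reproduced from the stated inputs alone. Across variants of the null variance, T = 1 gives 2184 to 2450, T = 12 gives 183 to 205 and T = 26 gives 85 to 95. An unstated exposure of about 6 to 6.5 gives 365 to 378 in some variants. That is a separate matter and does not decide this point. Below, the nominal 90% power is taken as given.

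**Inputs for the coach effect.**
- Analysed per arm: 187 × 0.9 = 168 (from the document).
- Number of coaches k: not in the documents; assumed 5, 10, 20 or 40.
- ICC: not in the documents; assumed 0.01 to 0.05.
- Equal caseloads and equal arm variances: assumed.

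**Formulas.**
- Design effect in the coached arm: DE = 1 + (168/k − 1) × ICC.
- Ratio of true to reported standard error: f = √[(1 + DE)/2].
- Power of an analysis using the correct standard error: Φ(3.2415/f − 1.96), where 3.2415 = 1.9600 + 1.2816.
- Two-sided type I error of the uncorrected test: 2 × [1 − Φ(1.96/f)].

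**Worked case**, 10 coaches and ICC 0.02: DE = 1 + 15.8 × 0.02 = 1.316; f = √(2.316/2) = 1.076; power = Φ(3.012 − 1.96) = 85%; type I error 6.9%.

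| Coaches | Per coach | f, ICC 0.01 to 0.05 | Power, correct SE | Type I error, uncorrected test |
|---|---|---|---|---|
| 5 | 33.6 | 1.08 to 1.35 | 85% to 67% | 6.9% to 14.6% |
| 10 | 16.8 | 1.04 to 1.18 | 88% to 78% | 5.9% to 9.7% |
| 20 | 8.4 | 1.02 to 1.09 | 89% to 85% | 5.4% to 7.2% |
| 40 | 4.2 | 1.01 to 1.04 | 90% to 88% | 5.2% to 5.9% |

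The last two columns belong to different analyses and should not be added together: the power loss appears if the standard error is corrected, the type I error if it is not.

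**Simulation check.** Gamma-Poisson counts were simulated with coach effects in one arm, 20,000 runs per scenario. A mean of 5.2 events per year (0.2 × 26) and a dispersion of 0.69 were assumed. Coverage of the nominal 95% interval, with no average effect and ICC 0.01 to 0.05, was 0.929 to 0.847 (5 coaches), 0.935 to 0.901 (10), 0.942 to 0.927 (20) and 0.947 to 0.939 (40). With ICC zero it was about 0.95. The simulated standard error ratios agree closely with f; for example, 5 coaches and ICC 0.05 gave 1.36 against 1.35.

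**The case against.** **The number of coaches is unknown.** The service has run since 2009 and covers three states, so the coach pool may be large. This stands: a reader might infer a small set of coaches, but no count is given. With 20 or more coaches and ICC of 0.02 or less, the formula puts the standard error ratio below 1.05.

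**A coach effect is not shown.** Shared training, common content and call audits may keep coaches alike. This also stands. A reader might infer that the primary interval is too narrow; the documents support this only on condition that coaches differ in effect.

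**Type I error depends on the null.** With individual randomisation, if coaching changes nobody's care-seeking, coaches cannot differ in effect and the type I error stays nominal. The inflated values arise only if coach effects vary around an average of zero and coaches are treated as a sample from a wider population. Inference limited to the coaches in the trial is defensible. This stands, so the type I figures are secondary here.

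**The article is condensed.** The three items are fidelity measures, not a data-transfer specification. A reader might infer that coach identity will not be obtained or could never be recovered; the documents do not say so. The service assigns the coaches and may hold the record, and an unseen statistical analysis plan could address clustering. What remains is that the article does fix the primary model, the dependence it recognises and the sample size basis, and none of these allows for coaches.

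**Coaches are matched to participants.** Caseloads will differ in patient mix, so a coach variance is not purely a coach effect. This stands and limits how the variance can be read.

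**Conclusion.** The point holds in conditional form. Coaching is nested within coach in the support arm only, the stated primary model and sample size make no allowance for it, and coach identity is not among the listed service data. If coaches differ in their effect on care-seeking, the reported interval is too narrow.

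The size runs from negligible (40 coaches, ICC 0.01: standard error 1% larger, power still about 90%) to serious (5 coaches, ICC 0.05: 35% larger, 67% power with the correct standard error). It rests on assumed coach numbers and ICC, equal caseloads, equal arm variances and 168 analysed per arm. At ICC zero there is no effect. No contradiction or false statement in the protocol is involved; this is a worthwhile, inexpensive improvement to the stated analysis.

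**What to change.** 1. In *Fidelity of the health coaching program*, add a coach identifier to the data the service supplies for each participant.
2. In *Statistical analysis*, pre-specify a sensitivity analysis of the primary rate ratio that allows for coach clustering in the support arm only. Use either a partially nested model or a cluster-robust variance with a small-sample correction. Treat each usual-care participant, and each support-arm participant who was never coached, as a cluster of one.
3. Report the number of coaches and the caseload sizes. State that the coach variance mixes coach effect with patient mix, because coaches are matched to goals and preference.

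The cost is one extra field in an existing data transfer, one extra model and possibly a wider interval in that analysis.
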